## *Secondary outcomes*

A new measure of user involvement in care planning (PROM) was developed in consultation with our user and carer advisory group during work stream one. The need for this measure was determined during the programme development grant as existing measures of user involvement were not deemed adequate by the advisory group. The newly developed PROM will be included as a secondary outcome to measure user and carer involvement in care planning. The new measure has excellent psychometric and scaling properties, by application to the Rasch model (Rasch 1960/1980). The scale is suitable for both service users and carers. Items are scored on a 5-point Likert scale from 'Completely disagree' to 'Completely agree'. Higher scores will reflect greater service user and carer involvement with care planning. Data from this study will provide further evidence of the acceptability, validity and sensitivity to change of this measure for this population.

Secondary outcome measures were determined using experts and a consensus discussion exercise with the user/carers advisory group. Key domains to measure were recommended by the advisory group based on proposals from the NIHR Mental Health Research Network (2010). The seven domains identified were quality of life; alliance/engagement; satisfaction; wellbeing; mental health symptoms; recovery and hope; and medication side effects. Six of these domains have one questionnaire selected for completion, whilst the domain 'satisfaction' has separate questionnaires for both service users and carers.

### *Satisfaction (service users)*

Verona service satisfaction scale (VSSS – EU-54, Ruggeri and Dall'Agnola (1993), is a specific setting, validated, multi-dimensional, self-administered scale for measuring patients' satisfaction with mental health services. There are seven dimensions; overall satisfaction, professional skill and behaviour, access, efficacy, types of intervention and relatives involvement. Subjects are asked to express their overall feeling about their experience of the mental health service they have been attending in the last year. Satisfaction ratings are on a 5 point Likert scale, with higher scores representing greater satisfaction. Global and subscale scores can be obtained. Reliability testing has shown that the VASS-EU has good internal consistency and stability (Ruggeri et al 2000).

### *Satisfaction (carers)*

Carers and Users' Expectations of Services – carer version (CUES-C, Lelliott et al 1999) will be used to measure carers' views of services. This is a self-rating scale consisting of 13 items each with two parts (A and B), totalling 26 questions. All questions are answered using a three point scale. There are three parts to the questionnaire; part A measures the impact of caring, part B measures the quality of support provided by carers and part C is a free text response for advice and help. Scores for each part range from 0 to 26, with higher scores representing more dissatisfaction and the need for more support. The scale has been found to be suitable to use to assess carers experiences (Lelliott et al 2003)

### Medication side effects

Glasgow Antipsychotic Side-effect Scale (GASS - Waddell and Taylor 2008) is a self-rating scale to detect the side effects of antipsychotic medication. The scale consists of 22 questions and scores range from 0 to 66. Higher scores reflect more frequent experience of side effects, with total scores providing three categories of severity (absent/mild side effects, moderate side effects and severe side effects).

### Well-being

Warwick Edinburgh Mental Wellbeing Scale (WEMWBS -Tennant et al 2007) is a short, psychometrically robust scale, which is easy to complete. It has 14 items scored on a 5-point Likert scale ranging from 'none of the time' to 'all of the time' based on experience over the past two weeks. Scores range from 14-70 and a higher score indicates a higher level of mental wellbeing.

### Recovery and hope

Developing Recovery Enhancing Environments Measure (DREEM -Ridway and Press 2004) is a self-report measure used to assess mental health recovery of people who receive mental health services. It is a 166-item questionnaire which is organised into 24 subscales (such as 'stage of recovery' and 'elements of recovery'), including a final section consisting of open ended questions. The scale is scored on a five-point Likert scale ranging from 'strongly agree' to 'strongly disagree', with low scores representing more positive experience. Dinniss et al (2007) found that DREEM was an effective and useful device for listening to the user voice.

## Mental health symptoms

Hospital Anxiety and Depression Scale (HADS, Zigmond and Snaith 1983) is a 14 item scale using a four-point Likert scale. Items are added to give two scores, one for anxiety and one for depression, with higher scores representing more severe symptoms. Scores range from 0 to 21 for both anxiety and depression. This is a well-used and validated measure (Barczak et al 1988, Bjelland et al 2002).

## Alliance/engagement

California Psychotherapy Alliance Scale (CALPAS - Gaston and Marmar 1994) is a 12-item, self-report questionnaire which provides a total score. It has four subscales: 'the patients capacity to work purposefully in therapy', 'the affective bond with the therapist', 'therapist's empathic understanding' and 'involvement and the agreement between the patient and therapist on the goals and tasks of treatment'. Each item is rated on a six-point Likert scale, with scores ranging from 12 to 84, with higher scores representing better alliance. It has good reliability and validity (Gaston 1991).

## Quality of life

World Health Organisation Quality of Life (WHOQOL-BREF - WHO 2004) is a 26-item questionnaire consisting of four domains (physical, psychological, social relationships and environment). Each question uses a five point Likert scale, ranging from a score of one to five, with higher scores representing more positive ratings. Total scores are commuted within each domain. It has been shown to demonstrate good reliability and validity (WHO 1997, The WHOQOL Group 1998)

## *Economic outcomes*

### Health Status

The EQ-5D-5L (Janssen et al 2012) measure will be used to assess health related quality of life for the economic analysis. The EQ-5D-5L, has two parts; part one, a five item questionnaire consisting of five dimensions (mobility, self-care, usual activities, pain/discomfort and anxiety/depression). Each dimension has three levels, ranging from no problems to severe problems. The five dimensions can be combined to describe the respondents' health state. Part two is a VAS which records the respondents self-rated health on a vertical VAS scale, where the end points are

labelled, 'best imaginable health state' and worst imaginable health state'. This information is used as a quantitative measure of health outcome as judged by the individual respondents.

### Service Use Questionnaire

A measure of health service contacts (service use questionnaire) is required to allow identification of service users in the intervention arm who have had contact with a trained worker. Although this will be used to assess receipt of the intervention and the causal pathway rather than cost per se, the measure will be derived from the economic analyses.

### *Allocation of outcome measures*

### Cohort Sample

#### Service Users:

- Demographic data will be collected at baseline.
- Primary Outcome – The HCCQ will be administered to the cluster cohort sample at baseline and at the six month follow-up.
- Secondary Outcome – the following seven measures will be administered at baseline and six months: VSSS-54, GASS, WEMWBS, DREEM, HADS, CALPAS-12, WHOQOL-BREF, along with the PROM.
- Economic Outcome – the EQ-5D-5L and the Service Use questionnaire will be administered at baseline and at the six month follow-up.

This information will be collected via a face to face method. As the 'cluster cohort' assessment is more burdensome, service users will receive a £10 voucher for their time after completion of the interview at six months.

#### Carers:

- Demographic data will be collected at baseline.
- Secondary Outcome – The PROM will be administered to the cluster cohort sample at baseline and at the six month follow-up. The CUES-C and the WHOQOL-BREF will also be administered at baseline and at the six month follow up
- Economic Outcome – The EQ-5D-5L will be administered at baseline and at the six month follow up.

This information will be collected via a postal method. Carers will receive a £5 voucher following receipt of the questionnaires at the six month time point.

## Cross-section Sample

### Service Users:

- Demographic data will be collected at the six month time point.
- Primary Outcome – The HCCQ will be administered at the six month time point only.
- Secondary Outcome – PROM
- Economic Outcome - The EQ-5D-5L and the service use questionnaire will be administered at the six month time point only.

This information will be collected via a postal method. All respondents will receive a £5 high street voucher if they provide their name and postal address. Names and addresses will be requested on a separate from the questionnaire.

There will be no collection of carer information in the cross-sectional part of the study.

Table 1 shows the list of measures to be used, with which respondents, and at what time points.

**Table 1 Summary of Outcome Measures**

| Outcome measures  |                            | BASELINE                  |                    | 6 MONTH FOLLOW UP         |                    |                                  |
|-------------------|----------------------------|---------------------------|--------------------|---------------------------|--------------------|----------------------------------|
|                   |                            | Service Users
(cohort) | Carers
(cohort) | Service Users
(cohort) | Carers
(cohort) | Service Users
(cross-section) |
| Primary Outcome   | Autonomy support           | HCCQ-10                   |                    | HCCQ-10                   |                    | HCCQ-10                          |
|                   | User and carer involvement |                           | EQUIP PROM         |                           | EQUIP PROM         |                                  |
| Secondary Outcome | User and carer involvement | EQUIP PROM                |                    | EQUIP PROM                |                    |                                  |
|                   | Satisfaction               | VSSS-54                   | CUES-C             | VSSS-54                   | CUES-C             |                                  |
|                   | Medication side effects    | GASS                      |                    | GASS                      |                    |                                  |
|                   | Well-being                 | WEMWBS                    |                    | WEMWBS                    |                    |                                  |
|                   | Recovery and hope          | DREEM                     |                    | DREEM                     |                    |                                  |
|                   | Mental health symptoms     | HADS                      |                    | HADS                      |                    |                                  |
|                   | Alliance/engagement        | CALPAS-12                 |                    | CALPAS-12                 |                    |                                  |
|                   | Quality of life            | WHOQOL-BREF               | WHOQOL-BREF        | WHOQOL-BREF               | WHOQOL-BREF        |                                  |
| Economic Outcome  | Health status              | EQ-5D-5L                  | EQ-5D-5L           | EQ-5D-5L                  | EQ-5D-5L           | EQ-5D-5L                         |
|                   | Service use                | Service use               | Service use        | Service use               |                    | Service use                      |

|  |  |               |  |               |  |               |
|--|--|---------------|--|---------------|--|---------------|
|  |  | questionnaire |  | questionnaire |  | questionnaire |
|--|--|---------------|--|---------------|--|---------------|

## **Study 7**

N/A

## **Analysis**

## **Study 5**

### *Statistical analysis*

A draft statistical analysis plan for primary and secondary outcomes, including sub-group analyses will be presented to the Programme Steering Committee prior to the commencement of the data analysis. Analysis of outcomes will follow intention-to-treat principles: outcome data will be sought and included in the analysis for all service users irrespective of receipt of the intervention or completion of care planning during the time scale of the EQUIP trial.

Standard data checking procedures will be used as part of the data cleaning procedure prior to locking the database and linkage to group allocation. We will then model the pattern of missing data in terms of baseline characteristics of service users and treatment allocation to check for differential non-response. Depending on the patterns of missing data we may at this point choose to use multiple-imputation with deletion. This may also be used to inform possible sensitivity analyses for missing data assumptions.

For the cluster cohort study the intervention effects for the primary outcome (HCCQ) and secondary outcome measures will be estimated using a linear mixed model with a random intercept for community teams. The baseline value of the outcome will be used as a covariate together with other covariates pre-specified in the statistical analysis plan. The same statistical modelling procedure will be used for estimation of the intervention effect in the cluster cross-sectional study using a restricted set of covariates. Full detail of covariates for each model will be confirmed in the statistical analysis plan. For the primary outcome we will estimate and present the treatment effect for the cohort and cross-sectional designs separately. We will then test for heterogeneity of the treatment effect and present this pooled estimate as a secondary outcome.

### *Economic analysis*

A cost effectiveness acceptability analysis will be conducted, from the perspectives of health and social care providers and service users, the key stakeholders in treatment decisions. The time horizon for the primary economic analysis will be at scheduled follow up (six months). Data on service use and health status (EQ-5D-5L) for the economic analysis will be collected for all participants at baseline and follow-up.

Data about the use of primary and community care based services will be collected by questionnaire completed by interview with the service users at the baseline and six month follow up assessments (cohort group). This is to ensure completeness of data collection and help to ensure that any questions or uncertainties about what should be reported can be addressed by the researcher completing the assessment. Data will also be collected from the cross-sectional group at the six month time point via the postal survey.

The service use questionnaire will ask for information about whether hospital inpatient and outpatients services have been used and if so, the name of the hospital, and this will be checked via records held by the case manager electronic record systems (with patient consent).

An economic patient questionnaire (service use questionnaire) to collect the service use information from service users will be adapted from those used in previous mental health evaluations. Service users will be asked for information about the number of care planning meetings they have attended. Data will also be collected from health records (with consent) about the resources (staff and facilities) used in the care planning process. The data from the service use questionnaire will be combined with the data in the health records to allow a detailed description of the service use and costs associated with care planning.

The time and expenses of service users, carers and staff involved in providing and receiving the training intervention will be documented along with details of facilities used. These data will be used to estimate the total cost of the training package. For the primary analysis, the cost of the training package will be allocated to trial participants by dividing the total cost by the number of participants randomised to the intervention group. This assumes that the investment in the training intervention lasts for six months (and has no impact after that time) and will only benefit the staff

trained and the participants in the trial. This may over-estimate the costs of the training package if the training has a longer effect on the staff trained and/or the staff trained apply their training to more participants than they see in the trial. The training may also have a wider effect than just on the staff trained and change care planning/service provision for wider group of staff. The effect (on the cost effectiveness of the intervention) of changing assumptions about the duration of effect and number of service users/carers affected will be explored in sensitivity analyses.

The main measure of health benefit will be the quality adjusted life year (QALY), in line with the perspective adopted and NICE guidelines (NICE 2013). QALYs will be estimated from survival and health status measured by the EQ-5D-5L (Brooks 1996, Herdman et al, 2011, Janssen et al 2012). The EQ-5D-5L is a validated generic health status measure, used in national health surveys in the United Kingdom and in clinical trials in mental health, covering five domains (mobility, self-care, usual activity, pain/distress, and anxiety/depression). The EQ-5D-5L has been used extensively in mental health evaluations and demonstrated to identify small but consistent differences between groups. It correlates well with clinical outcome measures and has the potential to capture the impact of an intervention on physical as well as mental health (Davies et al 2007; Davies et al 2008; Ntais et al 2013). The EQ-5D-5L is designed as a self-report measure and will be completed by trial participants at baseline and follow up.

The five level version will be used (no problems, slight problems, some problems, severe problems or unable to do activity). Utility values, that reflect preferences for different health states, will be derived from the published utility tariffs developed for the 5 level instrument. QALYs will be estimated as:

$$QALY = \sum [(U_i + U_{i+1}) / 2] \times (t_{i+1} - t_i)$$

where U = utility value and t = number of days between assessments.

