#### Within trial primary analysis

The primary measure for the economic analysis will be the incremental cost effectiveness ratio (ICER). Accordingly, no statistical tests of differences in mean costs or outcomes will be conducted. The ICER will be estimated as the:

$$\frac{\text{Cost}_{\text{intervention}} - \text{Cost}_{\text{usual care}}}{\text{Utility}_{\text{intervention}} - \text{Utility}_{\text{usual care}}}$$

The estimates of incremental costs and outcomes from the regression will be bootstrapped to simulate 10,000 pairs of net cost and net outcomes of the intervention group for a cost effectiveness acceptability analysis, as recommended by NICE for health technology appraisals (National Institute for Clinical Excellence, 2013). These simulated data will be used to estimate the probability that service user/carer led training and care planning is cost effective compared to usual care.

This approach re-values effects or benefits in monetary terms. However, in the UK there is no universally agreed monetary value for the types of benefit measures used in cost effectiveness analyses. An approach used in health care is to ask the question: what is the maximum amount decision makers are willing to pay to gain one unit of benefit? The simulated net utility values were revalued using a range of maximum willingness to pay values from £1 to £30,000 to gain one unit of outcome, based on the range of willingness to pay values implied by NICE decisions (Rawlins et al, 2004).

The data for the cost effectiveness acceptability curve will be derived by first revaluing each of the 10,000 net outcome scores from the bootstrap simulation by a single WTPT. This is repeated for each WTPT. A net benefit statistic (NB) for each pair of simulated net costs and net outcomes for each WTPT can then be calculated as

$$NB = (O * WTPT) - C, \text{ where } O = \text{net outcome score and } C = \text{net cost.}$$

This calculation is repeated for each WTPT. Cost-effectiveness acceptability curves plot the proportion of bootstrapped simulations where the net benefit of an intervention is greater than zero for each WTPT (Fenwick et al, 2001; Sendi et al, 2001; Hoch et al, 2002; Briggs et al, 2001).

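### The printed QALY formula gives quality-adjusted days and the printed ICER divides by a utility difference, so neither yields the QALY that the protocol names as its measure of benefit

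*Protocol*

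**What the plan says.** The Economic analysis section states the intended unit: "The main measure of health benefit will be the quality adjusted life year (QALY"), and links that choice to NICE guidance. It then prints a QALY as the sum, over successive assessments, of the mean of two adjacent utilities multiplied by a difference in t, "where U = utility value and t = number of days between assessments". Nothing in the protocol divides by the number of days in a year.

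Within trial primary analysis makes the ICER the primary economic measure. It prints the ICER as the difference in cost between arms over the difference in utility between arms. For the acceptability curve, it states of the bootstrap results: "net utility values were revalued using a range of maximum willingness to pay values from £1 to £30,000 to gain one unit of outcome". Elsewhere in that sentence the figures are described as "based on the range of willingness to pay values implied by NICE decisions". The net benefit statistic is net outcome times the willingness-to-pay value, minus net cost.

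Later text in the same section, and Within trial sensitivity analyses, again speak of costs and QALYs.

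On the instrument, Health Status (under Economic outcomes) says of the EQ-5D-5L: "Each dimension has three levels, ranging from no problems to severe problems". Economic analysis specifies the five-level version and the tariff developed for it.

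**The concern.** One willingness-to-pay range is applied to an outcome whose unit appears in three forms: a QALY in the text, a quality-adjusted day in the QALY formula, and a utility point in the ICER and the acceptability step. A monetary value per unit means something only when the unit is fixed.

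The definition of t is also malformed. It is described as the gap between assessments, which is already an interval, yet the formula takes differences of it.

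Cost-effectiveness is a stated objective of Study 5. The protocol rules out significance tests on mean costs or outcomes in this analysis, so the ICER and the acceptability curve carry the whole economic conclusion. If the formulas are followed as printed, both are on the wrong scale.

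**Working it through.** The protocol gives no numerical QALY, ICER or net benefit, so there is no figure to reproduce. The check is one of units.

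**Inputs from the protocol**
- Horizon six months, with utility measured at baseline and follow-up (Economic analysis). I take this as 182.625 days, or 0.5 year at 365.25 days per year.
- t in days; ICER denominator a utility difference; willingness to pay £1 to £30,000 per unit; net benefit NB = O × W − C, with O the net outcome, W the willingness to pay and C the net cost.

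**Assumed, because the protocol gives no values:** the follow-up utility difference dU and the net cost C.

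**1. QALY formula as printed**
- Constant utility 0.70: 0.70 × 182.625 = 127.8, against 0.70 × 0.5 = 0.35 QALY.
- Full health: 1 × 182.625 = 182.6, against 0.50 QALY.
- The ratio is 365.25 in every case. On this scale, £30,000 per unit equals 30,000 × 365.25 = £10,957,500 per QALY.

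**2. ICER denominator as printed**
- Equal baselines, linear build-up: (0 + dU)/2 × 0.5 = 0.25 dU QALYs. The trapezoidal rule gives this result with two assessments and equal baselines.
- Constant difference throughout: dU × 0.5 = 0.5 dU QALYs.
- £30,000 per utility point therefore equals 30,000/0.5 = £60,000 to 30,000/0.25 = £120,000 per QALY. The scale error is a factor of 2 to 4, depending on trajectory.

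**3. Where the £30,000 conclusion changes (utility reading only)**

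NB is positive when C is below 30,000 × O. The limit on C is 30,000 dU on utility, 7,500 dU on QALYs with linear build-up, and 15,000 dU on QALYs with a constant difference. Net costs between the QALY limit and the utility limit get the opposite conclusion.

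| Assumed dU | Limit, QALY linear | Limit, QALY constant | Limit, utility |
|---|---|---|---|
| 0.01 | £75 | £150 | £300 |
| 0.02 | £150 | £300 | £600 |
| 0.04 | £300 | £600 | £1,200 |
| 0.05 | £375 | £750 | £1,500 |

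**4. One worked case, dU = 0.04 and C = £500 (both assumed)**
- Utility: 500/0.04 = £12,500 per point; NB at £30,000 = 1,200 − 500 = +£700.
- QALY, linear: 500/0.010 = £50,000; NB = 300 − 500 = −£200.
- QALY, constant: 500/0.020 = £25,000; NB = 600 − 500 = +£100.

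The sign changes under linear build-up but not under a constant difference at this cost.

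**5. Direction**

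Inflating O raises NB when O and C are both positive, so cost-effectiveness is overstated for a health gain at extra cost. When both are negative, it lowers NB. When one is positive and the other is not, the sign of NB does not depend on the scale of O.

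**The case against.** The strongest reply is that the intent is plain. The text names the QALY, labels the formula as a QALY and returns to costs and QALYs afterwards. A six-month total near 128 is impossible as a number of life years, so an analyst would notice the day error at once. The net benefit text also uses generic words for outcome and benefit, so *utility* may be loose labelling. The sensitivity analyses reuse the ICER with the clinical primary outcome, which may explain some of that generic wording. An analysis plan that is not shown could settle the unit.

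Much of this stands. A reader might infer that the analysis would be run on the wrong scale, or that a 365-fold error would reach the report. The protocol does not support that, and the day error reveals itself.

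What does not fall away is the utility denominator. Economic analysis defines U as a utility value and keeps it distinct from the QALY built from it, and Within trial sensitivity analyses also separates the two. An ICER per utility point gives plausible-looking figures, so the slip could pass unnoticed. Nor is this a detail left for later: the protocol writes out the formulas, the units and the range itself, and they conflict.

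**Conclusion.** The point holds as an error in stated formulas that should be corrected before analysis. It does not touch the clinical primary outcome or its effect estimate.

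Its size is a fixed factor of 365.25 for the QALY formula. For the ICER denominator it is a factor of 2 to 4, the two ends resting on a constant difference and on linear build-up from equal baselines. These factors do not depend on the assumed cost or utility gain. The money bands do.

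Some stronger readings are tempting and not supported:
- **That the two faults multiply.** They are alternative denominators, and only one can be in use.
- **That the utility error is always fourfold.** It is twofold if the difference is constant.
- **That the conclusion reverses for any net cost from £300 to £1,200.** That band holds only for the utility reading, dU = 0.04 and linear build-up. With a constant difference it is £600 to £1,200, and it scales with dU.
- **That the ICER itself is set against £30,000.** The range enters through net benefit and the acceptability curve; the unit fault is the same there.
- **That the three-level description of the EQ-5D-5L adds to the unit problem.** It is a clerical slip with no effect on units.

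**What to change.** - Economic analysis: define t as the time of each assessment in years, that is, days since baseline divided by 365.25. The differences in the formula are then intervals in years and the result is a QALY.
- Within trial primary analysis: replace utility with QALY in both terms of the ICER denominator, and refer to net QALYs in the step that applies the £1 to £30,000 range.
- Separately, as a minor clerical correction, change the number of levels in Health Status to five, to agree with Economic analysis.

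The cost is wording only. No new data, assessments or change of design are needed.
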